### RCT design

The RCT is designed as an investigator-initiated, randomised, two-arm, assessor-blinded, multi-center, waiting list-controlled superiority trial. The allocation ratio to active and control condition is 1:1. The participants (*n* = 300) will be randomised to active condition (REWRITALIZE plus standard treatment) or waiting list control condition (standard treatment) (see Randomisation below). As it is a waiting list control group, the persons randomised to the control group will be invited to participate in a creative writing group after the last assessment (within one year). To ensure high methodological quality, the trial is designed and will be reported according to the SPIRIT 2013 Statement and the modified CONSORT 2017 criteria for non-pharmacological trials [15, 17]. Data will be collected at baseline, at the end of the intervention (approximately 4.5 months after baseline) and six months after the end of the intervention (approximately 10.5 months after baseline). A flow chart of the study is provided in Fig. 2.

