### Outcomes and assessments

#### Baseline characteristics

Baseline characteristics of the participants are collected through self-report and register data; see Table 1. The baseline characteristics are collected to ensure that the active and control groups do not differ on any potentially biasing characteristics. For the pilot RCT the PSE will be administered for diagnostic validation.

**Table 1 Tab1:** Participant characteristics

Variable	Source of collection
Age	Self-report
Sex	Self-report
Employment status	Self-report
Highest education	Self-report
Diagnoses	Register
Time since diagnosis	Register
Earlier use of mental health services	Register
Prior admissions (#)	Register
Antipsychotics	Register
Suicide attempt	Register
Admitted for alcohol and drug abuse	Register
Present state examination (pilot RCT)	Clinician rated

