#### Sample size and power calculations

The minimum sample size is calculated based on the ability to detect a minimal but clinically significant difference between the active intervention group and the control group in the primary personal recovery QPR measure. The minimal clinically significant difference between the study groups has been estimated to 4 points [53]. Based on trials in similar populations, we assume a standard deviation of 10 in the study population, which corresponds to an effect size of Cohen’s* d* = 0.4 [104, 114]. To achieve a statistical power of 90% at a significance level of 5%, a total of 266 participants must be included in this study to detect a difference: 133 in each group. Based on the needed participants, power calculations for secondary outcomes were calculated and are presented in Table 6. Because of the relatively high drop-out rate in the pilot study and similar studies [64, 110], we will plan for a sample size of 150 participants in the active group and 150 participants in the control group. This should hence allow for at least a 90% power of finding a minimally clinically significant difference in the primary measure, i.e., the QPR measure of personal recovery.

**Table 6 Tab6:** Power

**Outcome**		**Measure**	**Alpha**	**Mean diff**	**SD**	**Cohen’s *****d***	**Power**	***n***	**Mean diff source**	**SD source**
*Primary*			0,05							
	Personal recovery	QPR		4	10	0,40	0,9	266	[53]	[114]
*Secondary*										
	Connectedness	TBS	0,05	14	14	1	1	266	[60]	[60]
	Self-efficacy	SEPRS	0,05	x^a^	x	0,40	0,9	266		
	Functioning	WSAS	0,05	5	7	0,71	1	266	[69]	[69]
	Quality of life	MANSA	0,05	4	11	0,36	0,83	266	[11]	[11]
	Overall mentalising	MentS	0,05	8	12	0,66	1	266	[29]	[29]
	Alexithymia	TAS	0,05	7	11	0,63	1	266	[66]	[47]

See Table 5 and the assessment tool section for outcome measure abbreviations

^a^Power estimates for measures for which no relevant mean difference was identified are based on a moderate to small effect size of Cohen’s* d*=0.4

For the pilot RCT no calculation of sample size has been made as the primary aim for a pilot RCT is to explore design uncertainties before proceeding to a future RCT [35], here feasibility of chosen measures.

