#### Data analyses

The main outcome measure is personal recovery measured by QPR. To test the research hypothesis, the differences at follow-up between the active intervention group and the control group will be analysed using independent-samples t-test⁠. Effect sizes to judge clinical relevance will be estimated by Cohen’s d [19]. All variables are continuous. Secondary and exploratory measures will be tested by the same means. The significance level is set to 0.05 for all measures. If there, despite randomisation, are differences in any baseline measure between active and control groups, these differences will be adjusted for in the comparison between active and control groups using general linear models.

Data analyses will be based on the intention-to-treat principle. Data from all participants will thus be included in the analyses. In accordance with the principle, missing data from the follow-up will be imputed using multiple imputations by means of Markov Chain Monte Carlo methods in Stata. All co-variates of supposed prognostic significance will be used to impute a distribution of missing data. A prerequisite for multiple imputation is that data are missing at random. This will be examined by various means, e.g. by comparing prognostic baseline characteristics between the participants for whom follow-up data are missing and the participants for whom follow-up data have been collected.

As a supplementary analysis, the differences at follow-up between the active and control groups will be analysed including only observed data, i.e. data for whom follow-up data have been collected. A detailed statistical analysis plan will be prepared and uploaded to clinicaltrials.gov before initiating analyses.

For the pilot study mean, standard deviation, within and between group differences on the outcome measures will be calculated.

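### The primary QPR model is chosen from observed baseline imbalance, so the primary estimate is not fixed in advance; the rule is conservative and wastes efficiency

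*Protocol article*

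**What the plan says.** In the protocol article, Data analyses makes an independent-samples t-test at follow-up the test of the research hypothesis and applies the same method to secondary and exploratory outcomes. It sets the level: "The significance level is set to 0.05 for all measures". It then adds a conditional step: "If there, despite randomisation, are differences in any baseline measure between active and control groups, these differences will be adjusted for", using general linear models. The section gives no threshold for a difference and no covariate list. It does not say whether the adjusted result replaces the t-test or accompanies it.

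The Baseline characteristics section shows the same thinking: "The baseline characteristics are collected to ensure that the active and control groups do not differ on any potentially biasing characteristics".

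Three other statements bear on the point. Randomisation is stratified by site (Assignment of interventions). Researchers analyse with arms coded A and B (Blinding). A detailed SAP is promised on the trial registry before analyses start (Data analyses); it is not available here.

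**The concern.** The model for the primary comparison depends on which baseline variables happen to differ between the arms. With concealed randomisation those differences are chance, so testing for them answers no useful question. Imbalance is also the wrong criterion for adjustment. What matters is whether a variable predicts the outcome, and an imbalance test says nothing about that. Baseline QPR, the same questionnaire measured earlier, would be ignored when balanced, whereas a variable unrelated to QPR could enter the model because it was imbalanced.

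The word 'differences' is also undefined. Read literally, two arms almost never have identical baseline values, so everything would be adjusted for. Read as a significance test, the covariate set varies by chance from one trial to the next. In either case a reader cannot tell from the protocol which estimate will be the primary one.

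**Working it through.** **1. The plan's own figure.** The inputs, from Sample size and power calculations and RCT design, are: "The minimal clinically significant difference between the study groups has been estimated to 4 points"; "we assume a standard deviation of 10 in the study population"; "The allocation ratio to active and control condition is 1:1"; "To achieve a statistical power of 90% at a significance level of 5%, a total of 266 participants must be included in this study". Sidedness is not stated; two-sided is assumed.

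n per arm = 2 × (1.960 + 1.282)² × 10² / 4² = 131.3, so 132. The t-distribution gives 132.3, so 133 per arm and 266 in total, as stated. A one-sided test would give 108 per arm (216), which does not fit. Normal-approximation power of the t-test at 133 per arm is Φ(0.4 × √(133/2) − 1.960) = Φ(1.302) = 90.4%.

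**2. How often the rule fires.** Assume that a difference means p<0.05. For K independent measures the chance of at least one is 1 − 0.95^K.
- Seven outcome scales only: 1 − 0.95^7 = 30%.
- Eleven baseline characteristics plus seven scales in Table 5, 18 in all: 1 − 0.95^18 = 60%. With pairwise correlation 0.2 (assumption), simulation gives about 56%.

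**3. Type I error of the two-stage rule.** Take baseline QPR as the only candidate. The protocol gives no baseline-to-follow-up correlation r; 0.3 to 0.7 is assumed. Under the null the t-test rejects 5% of the time and the trigger fires 5% of the time. In triggered trials the t-test would reject at a raised rate a, but ANCOVA, which rejects at 5%, replaces it. So the error rate is approximately 5% − 5% × a + 5% × 5%.

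| r | a (simulated, 133 per arm) | Error by formula | Error simulated |
|---|---|---|---|
| 0.3 | 9.4% | 4.8% | 4.7% |
| 0.5 | 15.7% | 4.5% | 4.3% |
| 0.7 | 33.3% | 3.6% | about 3.5% |

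Repeat simulations at r = 0.7 ranged from 3.4% to 4.0%. With 18 candidates (pairwise correlation 0.2) the rates were 4.8%, 4.3% and 3.4%. At r = 0 the rule holds about 5%. The departure is therefore downward.

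**4. Power at 133 per arm for 4 points, SD 10.** A fixed ANCOVA reduces the residual SD to 10√(1 − r²), so its power is Φ(3.262/√(1 − r²) − 1.960).

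| r | Fixed ANCOVA, formula | Fixed ANCOVA, simulated | Two-stage rule, 18 candidates, simulated |
|---|---|---|---|
| 0.3 | 92.8% | 93.0% | 90.6% |
| 0.5 | 96.5% | 96.3% | 90.9% |
| 0.7 | 99.5% | 99.5% | 91.6% |

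With baseline QPR as the only candidate, the two-stage rule has about 91–92% (repeat runs lie between 90% and 92%), and a fixed ANCOVA has 93–99.6%. The simulated type I error of the fixed ANCOVA was 4.5–5.1%.

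**5. If the wording were used to choose a result.** Taking the better p-value only in triggered trials gives about 5% with baseline QPR as the sole candidate and 5.4–6.0% with 18 candidates. Taking the better of t-test and ANCOVA in every trial, whether or not the trigger fired, gives roughly 7–9% for r of 0.5 to 0.7.

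**The case against.** The strongest defence is that the rule, applied as printed, does not endanger the false-positive rate: it is conservative and still meets the 90% power target. A detailed SAP is promised before analysis and may define the trigger or remove it. The A/B coding makes it harder to choose a model because it favours the intervention. The text can also be read as one analysis replacing the other, not as two results to choose between.

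Most of this stands, and it rules out several stronger readings that a reader might infer.
- *The 5% level is inflated.* The printed rule does not do this. Inflation needs an analyst to exploit the undefined word, and the 7–9% figure needs the trigger to be ignored altogether.
- *The model will switch in 60% of trials.* That counts all 18 baseline variables as measures and treats them as independent. Elsewhere in Data analyses 'measures' refers to outcome scales, and on that reading the figure is 30%.
- *An untriggered imbalance biases the estimate.* At 150 per arm an imbalance just below the assumed trigger is 1.968 × 10 × √(2/150) = 2.27 points. With r of 0.5 to 0.7 it shifts the unadjusted estimate by 1.1 to 1.6 points. That is a conditional worst case; over randomisation the t-test is unbiased and holds its level.

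The defence does not remove the rule. Analysts working with A and B still see the imbalance between A and B. An SAP that follows this protocol would inherit the rule. The fault lies in something the protocol states, not in a detail left for later.

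**Conclusion.** The point holds as one of efficiency and pre-specification. The protocol lets chance imbalance decide the covariates of its primary model and does not define the trigger, so the primary estimate is not fixed in advance. Reading a difference as p<0.05, with baseline QPR as the sole candidate and r between 0.3 and 0.7, the true type I error is about 4.7% down to 3.5%. Compared with always adjusting, the rule gives up roughly 2 to 8 percentage points of power at 133 per arm. The threshold, the candidate set and the correlation are assumptions; the protocol gives none of them. The stated sample size reproduces and the stated power is still reached, so the trial's validity is not in question. This should be fixed, but it is not a fatal flaw.

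**What to change.** Replace the conditional sentence in Data analyses. The primary QPR analysis becomes a linear model with treatment, the baseline value of the outcome and site (the stratification factor), fitted whatever the observed balance. Secondary and exploratory outcomes follow the same form, each with its own baseline value. Any further prognostic covariate should be named before unblinding.

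Reword Baseline characteristics so that these variables are described by arm without significance tests. Any model that adds covariates because they looked imbalanced should be labelled a sensitivity analysis.

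The cost is wording only. Baseline QPR and site are already collected and the sample size need not change. The change should be made, and carried into the SAP, before data are unblinded.

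### Covariates in the primary QPR comparison are selected by chance baseline imbalance, so the primary model is not fixed and power from baseline QPR is given away

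*Protocol article*

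**What the plan says.** In the protocol article, Data analyses, the primary test is stated first: "the differences at follow-up between the active intervention group and the control group will be analysed using independent-samples t-test". A few sentences later comes the covariate rule: "If there, despite randomisation, are differences in any baseline measure between active and control groups, these differences will be adjusted for in the comparison", to be done "between active and control groups using general linear models". The section does not list covariates, does not say what counts as a difference (a p-value, a standardised difference or judgement), and does not say whether the t-test or the adjusted model is then the primary result. Secondary and exploratory outcomes follow the same approach, and "The significance level is set to 0.05 for all measures".

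The Baseline characteristics section shows the thinking behind the rule: "The baseline characteristics are collected to ensure that the active and control groups do not differ on any potentially biasing characteristics".

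Three other statements bear on the point. Assignment of interventions says that randomisation is stratified by site, but Data analyses does not name site as a covariate. Blinding says that someone outside the team extracts the data at study completion, with arms coded A and B. Data analyses promises a detailed analysis plan before analysis starts.

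**The concern.** The trigger is the flaw. With concealed randomisation, differences between arms in variables measured beforehand are due to chance. A rule that adjusts for whatever turns out uneven therefore selects covariates on a criterion unrelated to whether they predict follow-up QPR. A strongly prognostic variable that is only mildly uneven is left out, and an irrelevant one that is clearly uneven goes in. The same section takes the better approach for imputation, where covariates are to be chosen for presumed prognostic value.

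Two things are at stake. First, the model behind the primary p-value is not known until the baseline table has been inspected, although the sample size was worked out for one particular test. Second, baseline QPR is probably the best available predictor of follow-up QPR, yet it enters only when it happens to be unbalanced. The precision it could give is then mostly lost, and the two-stage test does not have the error rate it is reported to have.

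**Working it through.** **Inputs from the protocol article.** Sample size and power calculations: "The minimal clinically significant difference between the study groups has been estimated to 4 points"; "we assume a standard deviation of 10 in the study population, which corresponds to an effect size of Cohen’s" d of 0.4; "To achieve a statistical power of 90% at a significance level of 5%, a total of 266 participants must be included", which is 133 per arm. Table 5 lists 11 baseline characteristics and 7 full-sample questionnaires (QPR, TBS, SEPRS, WSAS, MANSA, MentS, TAS), so 18 baseline variables.

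**Assumptions not in the document.** The trigger is p<0.05. The correlation r between baseline and follow-up QPR is 0.5 to 0.7. The other baseline variables do not predict QPR.

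**1. The plan's own figure.** n per arm = 2 × (1.960 + 1.282)² × 10² / 4² = 131.3, rounded up to 132. The t-based calculation gives 132.3, rounded up to 133, so 266 in total. The stated figure is reproduced. It is the sample size for the unadjusted t-test.

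**2. How often the t-test would be displaced.** With k independent variables, P(at least one p<0.05) = 1 − 0.95^k.
- All 18 variables: 1 − 0.95^18 = 0.60. With the seven questionnaires correlated 0.5 with each other, simulation gives about 0.55.
- The 7 questionnaires only: 1 − 0.95^7 = 0.30, or about 0.23 with the same correlation.

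**3. Size and power of the rule applied mechanically.** Monte Carlo, 133 per arm, 18 independent baseline variables, each screened at p<0.05, then a linear model with those selected (t-test if none). Size rests on 20,000 trials with no effect (standard error about 0.15 percentage points), power on 5,000 trials at d = 0.4 (about 0.4 points or less).

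| r | Size: t-test | Size: triggered rule | Size: baseline QPR always in | Power: t-test | Power: triggered rule | Power: baseline QPR always in |
|---|---|---|---|---|---|---|
| 0.5 | 5.0% | 4.3% | 4.9% | 89.9% | 90.6% | 96.2% |
| 0.6 | 4.8% | 3.7% | 4.6% | 89.9% | 90.6% | 97.7% |
| 0.7 | 5.0% | 3.7% | 5.0% | 89.9% | 90.9% | 99.4% |

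With the seven questionnaires correlated 0.5, the triggered rule has a similar size (about 3.5–4.6%) and power of about 91–92%. Looser triggers of 0.10 or 0.20, with independent variables and 150 per arm, give 2.9–4.2%.

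The rule is conservative for a simple reason. When baseline QPR is clearly uneven, which is when the t-test would often reject falsely, the rule adjusts and removes the error. When baseline QPR is even, the t-test is kept with a standard error that still carries the variance baseline QPR would explain, so it rejects too seldom.

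**4. Closed-form check on the last column.** Residual SD = 10 × √(1 − r²) = 8.66, 8.00 and 7.14. Power = Φ(4 / (SD × √(2/133)) − 1.96) = 96.5%, 98.3% and 99.5%, in line with the simulation.

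**5. What discretion could add.** If the trigger were chosen after the results were seen, taking the best of p<0.05, p<0.10 and p<0.20 gives a size of about 5.5–6% with correlated questionnaires. With independent questionnaires it stays near 5% (4.4–5.1%). Adding never adjusting as a fourth option raises the correlated figure to about 7.4–8.3%.

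**The case against.** **The 5% level is not shown to fail.** A reader might infer that the false-positive rate exceeds 5%. The text does not support that. With every fixed trigger tried, the size is below 5%. The 7.4–8.3% figure needs an analyst who runs four models, one of which never adjusts, and keeps the best. The protocol says that differences will be adjusted for, so it does not offer that fourth option. This objection stands: the demonstrable harm is miscalibration and lost power.

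**The count of 18 is one reading.** Table 5 separates baseline characteristics from outcome measures, and the rule speaks of a baseline measure, which could mean the seven questionnaires alone. On that reading the t-test survives in most trials. The stated purpose of the baseline characteristics favours the wider reading but does not settle it, and the p<0.05 trigger is not in the document. It therefore cannot be said that the t-test will most likely be replaced.

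**The trigger does not look at the outcome.** It uses baseline values and allocation, not follow-up QPR. That is correct. But data are extracted only at study completion, so the undefined criterion can still be settled with outcomes to hand.

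**Safeguards exist.** A/B coding limits steering towards a favoured arm, but it does not stop a choice by significance. The promised analysis plan may define the trigger, and its absence here is no fault. A defined trigger would still be the wrong selection principle, and that principle is what the article states.

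**Conclusion.** The point holds in a limited form. The article sets out a rule under which chance imbalance, not prognostic value, decides the covariates of the primary comparison, so the primary model is not fixed. On a p<0.05 trigger the t-test for which the trial was sized would give way in about 55–60% of trials (18 variables) or about 23–30% (7 questionnaires). Applied mechanically, the rule has a size of about 3–4.5% and power of about 91–92% at 266 participants and d = 0.4. Including baseline QPR in every case gives nominal size and about 96–99% power. All these figures rest on the assumed trigger, and the size and power figures also on an assumed QPR correlation of 0.5–0.7; neither is in the document. Inflation above 5% is a modest possibility that depends on discretion after results are seen. It is not a consequence of the rule as written. The plan should be changed, but the trial's validity is not in doubt on this ground.

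**What to change.** Delete the imbalance-triggered sentence in Data analyses. Before any follow-up data are extracted, name one covariate set for the primary model and use it whatever balance is observed: the baseline value of the outcome, and site because randomisation is stratified by it. Apply the same form to each secondary questionnaire with its own baseline value. Do not use baseline significance tests to choose covariates. Label any further model prompted by an observed imbalance as a sensitivity analysis that cannot replace the primary result.

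The cost is wording in the analysis plan. Baseline QPR and site are already recorded, so no participants, visits or data are added. Restating the purpose of the baseline characteristics as description of the sample and arms would be tidy, but it is optional and changes no result.

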### Participants

Participants in the RCT will be included in the study if they are over 18 and diagnosed with a severe mental illness, i.e., schizophrenia, schizotypal, delusional, and other non-mood psychotic disorders, bipolar disorder, severe depression, posttraumatic stress disorder, or borderline personality disorder (F2, F31, F32.2, F32.3, F33.2, F33.3, F43.1, F60.3). Forensic psychiatric patients will be excluded. In all, 30–34 groups, 15–17 active groups and 15–17 control groups, will be carried out with 8–10 participants in each group. Although power calculations (see below: Sample size and power calculations) set the minimum sample size to 266 and the RCT intention-to-treat principle reduces the threat of drop-out for power, we will aim to include 300 participants. Considering the relatively high drop-out rate in similar interventions [64, 110], the enhanced inclusion enables us to aim for a higher number of real, as opposed to imputed, follow-up data, and to minimise the risk to end up with low power if participants were to retract their informed consent.

Participants in the pilot RCT will be included in the study if they are between 18 and 35 and fulfil the criteria for a schizophrenia spectrum disorder (F20, F21) according to the Present State Examination [87, 115].

Participants will be recruited from outpatient clinics’ OPUS programs (early intervention program for first episode psychosis) and F-ACT (Flexible Assertive Community Treatment) at Mental Health Centres in Regions Capital and Zealand in Denmark [40, 75, 109].

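### Comparing baseline characteristics cannot examine the missing-at-random assumption, and agreement with the observed-data analysis would not support it either

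*Protocol article*

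**What the plan says.** The relevant text is in the Data analyses section of the protocol article. Missing follow-up data will be multiply imputed in Stata from all covariates thought to be prognostic, and MAR is named as the prerequisite. The article says MAR will be examined in several ways and gives one example: "comparing prognostic baseline characteristics between the participants for whom follow-up data are missing and the participants for whom follow-up data have been collected".

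One supplementary analysis is named: "the differences at follow-up between the active and control groups will be analysed including only observed data". A detailed SAP is promised before analysis starts.

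Four other places bear on the point:
- Participants explains the larger target of 300 partly by expected loss: "Considering the relatively high drop-out rate in similar interventions". Sample size and power calculations says the same of the pilot study. Neither gives a rate.
- Data collection says that everyone who has not withdrawn consent will be contacted for follow-up, including those who stop the group early, and that reasons for drop-out are recorded. It gives those reasons no role in the analysis.
- Table 2 shows QPR as a self-report measure, and Blinding says that participants know their allocation.
- RCT design makes the comparator a waiting list.

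**The concern.** MAR says that, given the observed data, the chance of a missing value does not depend on the value itself. Baseline characteristics are observed, so comparing them by follow-up status tests something else: whether missingness is related to those characteristics, which concerns missing completely at random. A difference does not refute MAR, because imputation can condition on the variables that differ. The absence of a difference does not support MAR, because drop-out may follow how participants fare after baseline.

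The observed-data comparison does not fill the gap. An unadjusted t-test on observed scores needs missingness to be unrelated to outcome within each arm, which is at least as demanding as MAR. When drop-out depends on the outcome, both analyses can be wrong by the same amount and agree with each other.

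What is at stake is the robustness claim for the primary result. With unblinded participants, a self-reported outcome and a waiting-list control, reasons for non-response that differ by arm are plausible. A report could describe MAR as examined and confirmed on evidence that cannot bear on it.

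**Working it through.** **1. The plan's own figure.** "The minimal clinically significant difference between the study groups has been estimated to 4 points", and "we assume a standard deviation of 10 in the study population". With two-sided alpha 0.05 (sidedness is not stated, so assumed) and 90% power, the normal approximation gives n per arm = 2 × (1.960 + 1.282)² × 10² / 4² = 131.4, rounded up to 132, or 264 in total. The t-test calculation gives 132.3, rounded up to 133, or 266 in total. The stated 266 reproduces and is not in dispute.

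**2. Loss that the target allows.** 1 − 266/300 = 11.3%. This is the only loss figure that can be derived from the article. The higher rates below are assumptions.

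**3. Size and direction of bias.** Let d be the fraction missing in an arm and k the number of points by which the true missing scores fall below their imputed values. That arm's mean is overstated by d × k, so

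bias in (active − control) = d_A × k_A − d_C × k_C.

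A shortfall in the active arm alone inflates the benefit, a shortfall in the control arm alone masks it, and equal products cancel. With a shortfall in one arm only, the absolute bias in QPR points is:

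| Missing in that arm | k = 5 | share of 4 points | k = 10 | share of 4 points |
|---|---|---|---|---|
| 11.3% | 0.57 | 14% | 1.13 | 28% |
| 20% | 1.0 | 25% | 2.0 | 50% |
| 30% | 1.5 | 38% | 3.0 | 75% |
| 40% | 2.0 | 50% | 4.0 | 100% |

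**4. Tipping point.** With 150 per arm and SD 10, the full-data standard error is 10 × √(2/150) = 1.155 and the critical difference is 1.96 × 1.155 = 2.26. An estimated difference of 4 loses significance when d × k in the active arm exceeds 4 − 2.26 = 1.74. The required shortfall is about 15.4 points at 11.3% missing, 8.7 at 20%, 5.8 at 30% and 4.3 at 40%. Missing data enlarge the standard error, so the true tipping points are somewhat lower.

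**5. Behaviour of the named check.** Simulation of 2000 trials per scenario, with 150 per arm, SD 10, true effect 0 and an assumed baseline to follow-up correlation of 0.5. Control drop-out was unrelated to anything. Active-arm drop-out was made to depend strongly either on the part of the outcome not explained by baseline, or on baseline alone. Regression imputation within arm stood in for the multiple-imputation point estimate.

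| Active-arm drop-out depends on | Missing, control / active | Baseline comparison p < 0.05 | Bias, imputed | Bias, observed data |
|---|---|---|---|---|
| outcome, not baseline (MAR false) | 20% / 27% | 5.3% | +2.5 | +2.5 |
| outcome, not baseline (MAR false) | 30% / 35% | 5.7% | +3.3 | +3.3 |
| baseline only (MAR true) | 20% / 27% | 99% | −0.01 | +1.5 |
| baseline only (MAR true) | 30% / 35% | over 99% | +0.01 | +1.9 |

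Where MAR fails, the check fires at about its nominal 5% and the two analyses agree on a biased answer. Where MAR holds, the check fires almost always although the imputed estimate is sound, and the two analyses disagree. The bias sizes, and the positive sign, come from the assumed drop-out model. That the check cannot separate the two situations does not depend on that model.

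**The case against.** The strongest reply has five parts.

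- **The comparison is only an example.** This is correct: the article leaves other means open, and a reader who took the comparison for the whole check would be reading too much in. But no other check on observed data could verify MAR either, so the sentence still promises what cannot be delivered that way.
- **An SAP is promised.** A reader might infer that the trial plans no analysis departing from MAR. The article does not support that, because the SAP is not shown and may contain one. Its absence here is not the point. The point is that the article states an unsuitable method, which an SAP could inherit.
- **Nothing hangs on the check.** No rule changes or drops the imputation according to its result, so the estimate is the same with or without it. Likewise, the observed-data analysis is called supplementary and is not offered as a test of informative drop-out. Both observations stand. What is affected is the claim of robustness, not the estimate. The biases above belong to any analysis that assumes MAR when MAR fails.
- **People who leave the group are still followed up.** This is a real safeguard, and stopping the intervention must not be equated with missing outcome data. Together with imputation from prognostic covariates it makes MAR more plausible. It does not test it.
- **The bias may be small or run the other way.** A reader might infer that the planned analyses are biased towards benefit. The documents do not support a direction: losing poorly faring controls would hide a benefit, and similar losses largely cancel. At 11.3% missing, a 5-point shortfall in one arm moves the result by only 0.57 points.

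**Conclusion.** The point holds as a correction of a stated method. The named baseline comparison cannot examine MAR, and agreement between the imputed and observed-data results would not show that drop-out is harmless. It does not show that the primary result will be biased, or in which direction.

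The possible size runs from minor to important. A 5-point shortfall in one arm costs 14% of the relevant difference at 11.3% missing and 38% at 30%. This rests on assumed shortfalls and, above 11.3%, on assumed rates, since the article calls drop-out relatively high without a figure. Because the rate is open and the outcome is self-reported by unblinded participants, the change is worth making before the SAP is fixed.

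**What to change.** Reword the sentence so that the baseline comparison describes who is missing and informs the choice of imputation covariates, and no longer serves to examine MAR.

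In its place, state that departures from MAR will be examined by a prespecified delta-adjusted multiple-imputation analysis of QPR at 4.5 months. Shift the imputed scores in the active arm alone, in the control arm alone and in both together, and report the shift at which the conclusion changes. The range of shifts and other details belong in the SAP.

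Impute separately by arm. Session attendance, recorded by the co-conductor (Adherence to the intervention), can enter the active-arm model only, because waiting-list participants have none during follow-up. The observed-data analysis can stay as a supplement, provided that its agreement with the imputed result is not presented as evidence for MAR.

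The cost is one reworded sentence and a few extra analysis runs in Stata. No new data are needed.
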